### Assessment of depression and quality of life

DASSThe DASS (Depression Anxiety Stress Scale) is a validated screening method and measures depression, anxiety, and stress levels in the past week [28].WHOQOL-BREF-DISThe WHOQOL-BREF-DIS is an instrument for recording the subjective quality of life. It covers the areas of physical and mental well-being, social relations, and the environment. The DIS module deals with questions about physical limitations [29]. It has been validated in patients with SCI and stroke.

### Questionnaire and interview on the individual patient care network and coordination of care

During the final visit, the study participants will receive a questionnaire to indicate the individual patient care network and the degree of coordinated care. The questions relate to diseases other than stroke/SCI, the visited health care providers as inpatient and during the last 8 months in the home environment, circumstances of the physical therapy (e.g. process of finding the appropriate therapist), aspects regarding quality of therapy care, the cooperation between family practitioner and physical therapist and missed services (supplementary file; questionnaire 2).

Afterwards the participants will be invited to join an interview to explore the context and connections of factors which might influence the respective care in the ambulatory sector. The participants will be interviewed via telephone according to an interview guide. Data of the entire study sample is not manageable; therefore a purposive sampling strategy will be employed. The selection of participants is based on written consent, age, sex, stroke/SCI, study center (local distribution over Germany), mobility parameters and functional impairment. The data analysis follows the concept of qualitative content analysis [30].

### Patient-reported treatment goal attainment

To record the prescriptions of physical therapy, a daily interview is automatically generated by the tablet application (Fig. 4). This so-called “evening query” starts with the recurring question of “How are you today?”, which can be rated on a 5-point ordinal scale. Next, the study participant is asked whether an appointment for physical therapy is scheduled the following day. If it will be the first session of a new prescription cycle, an 11-item (5-point ordinal scale for each item) questionnaire will pop up to select between 11 prespecified treatment goals (joint mobility, pain reduction, spasticity in both legs, strength and endurance, transfer, standing and balance, walking, wheelchair mobility, 3 items about mobility). If it will be the last session of a prescription cycle, the participant will be asked to evaluate the same 11 items. Moreover, the participant will be asked to rate the overall satisfaction of goal attainment on a 5-point ordinal scale. Where applicable, the query algorithm reminds the study participant to bring along the tablet to the next physical therapy session to ask for corresponding ratings by the therapist (supplementary file; questionnaire 3).

**Fig. 4 Fig4:**
[figure not shown]
Screenshots of the patient App on the tablet computer. Upper panel: “evening query”. Mid panel (left): the study participant is asked whether an appointment for physical therapy is scheduled the following day. Mid panel (right): If it will be the first session of a new prescription cycle an 11-item (5-point ordinal scale for each item) questionnaire will pop up (lower panel) to select between 11 prespecified treatment goals (e.g. pain reduction)

### Therapist-reported treatment goal attainment and treatment measures

Similarly, the physical therapists are asked and evaluated about treatment goals for the upcoming prescription cycle on this 11-item questionnaire via the tablet of the participant (joint mobility, pain reduction, spasticity in both legs, strength and endurance, transfer, standing and balance, walking, wheelchair mobility, 3 items about mobility). Additionally, at the last treatment session, the therapist will be asked about the treatment setting (controlled environment (e.g. physical therapy practice), real-life simulation environment (e.g. stairs in physical therapy practice), or real-life situation (e.g. participants’ home, public transportation) and the applied treatment measures (e.g. joint mobilization, endurance training, strength training, sitting balance, standing balance, gait training, transfer−/wheelchair-training, coordination). Finally, the therapist will be asked to quantify the training intensity (dose) on a visual analogue scale (supplementary file; questionnaire 4).

### Statistical procedures

Primary outcome (1), which represents the basis for the sample size calculation, will be analyzed using multiple linear mixed regression methods for repeated measures. For these regression analyses, the primary outcome (1) is defined as the change in the daily distance covered between baseline and final visit after 8 months. To account for day-to-day fluctuations as well as for acclimatization effects during the transition between acute rehabilitation and settling into the home environment, the baseline mobility measurement is defined as the daily distance averaged over the second week after start of mobility recording, i.e. day 8–14 after baseline (up to 6 weeks after discharge from acute rehabilitation). Because we expect a significant number of participants in older age groups with difficulties to master the required technology, this approach allows for an extra week of getting accustomed to the activity tracker technology in both groups. For the final mobility measurement, we will use the daily distance averaged over the final week prior to the last study visit. The utilization of such statistical models allows for adjustments of confounding variables (e.g. daily mobility at baseline, number of treatment sessions, or severity of the neurological disorder). Moreover, linear mixed models are also quite robust and statistically more powerful with respect to missing data of repeated measurements (under the assumption of missing at random). Additionally, hitherto not further prespecified statistical analyses on the repeated mobility measurements are planned (e.g. individual continuous trajectories, bouts of mobility).

As the main predictor variable for the primary outcome (1) and basis for our sample size considerations, we will use the primary outcome (2) “degree of participation” of the physical therapy, which has been carried out during the 8 months study period. The answers of the therapist at the end of each prescription cycle to the itemized questionnaire on the patient tablet are the basis for an evaluation of the “degree of participation” of therapy, ranging from 0 to 100% of all treatment session.

Primary outcome (3) focuses on the agreement of treatment goals between patients and therapists. The itemized questionnaires between patients and therapists will be analyzed by intraclass-correlation methods. The resulting correlation coefficients indicate the degree of agreement concerning treatment goals between patients and therapists. Resulting agreement measures can serve for further exploratory analyses (e.g. subgrouping, use as confounding/explanatory variable in exploratory regression analyses, use as explanatory variable for quality of life measures, etc.).

Primary outcome (4) represents goal attainment analysis related to either patients or therapists, respectively. Subjectively highly ranked treatment goals are subject to requery at the end of each prescription cycle. The requery is performed via itemized questionnaires. Sum scores of items (item on 5-point ordinal scale) indicate the degree of goal attainment. Results serve for further exploratory analyses, e.g. as explanatory variable for functional outcomes, quality of life measures, etc.).

Secondary outcomes are evaluated with descriptive analysis.

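### Primary outcome (1) is announced as a repeated-measures mixed model but defined as one change score per patient, so the cited robustness to missing repeated measurements is not available

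*Protocol article*

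**What the plan says.** All of the following is in the protocol article, Statistical procedures, unless noted.

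- **Model.** Primary outcome (1) "will be analyzed using multiple linear mixed regression methods for repeated measures".
- **Response for that model.** "the primary outcome (1) is defined as the change in the daily distance covered between baseline and final visit after 8 months".
- **The two ends of the change.** At the start, "the baseline mobility measurement is defined as the daily distance averaged over the second week after start of mobility recording". At the end, "For the final mobility measurement, we will use the daily distance averaged over the final week prior to the last study visit".
- **Adjustment.** Example confounders are "e.g. daily mobility at baseline, number of treatment sessions, or severity of the neurological disorder", so baseline distance is a candidate covariate.
- **Missing data.** As an advantage of the model, "linear mixed models are also quite robust and statistically more powerful with respect to missing data of repeated measurements", under missing at random.
- **Other tracker data.** Separately, "hitherto not further prespecified statistical analyses on the repeated mobility measurements are planned".

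The Sample size section repeats the change from baseline to 8 months as the primary endpoint and sizes the study with a simple linear regression. It adds that a mixed model, together with further positively correlated outcome measures, should raise power. It does not name those measures or their times.

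**The concern.** A mixed model for repeated measures draws its strength from several outcome rows per patient. When a late value is missing, the patient's earlier rows stay in the likelihood and, through the within-patient correlation, carry information about the missing value. That is what makes the analysis valid under missing at random.

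The stated response removes those rows. Baseline and final week are subtracted before the model is fitted, and everything between them is assigned to other analyses. The article therefore claims a protection that its own outcome definition takes away.

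This matters because gaps in tracking are foreseeable. Statistical procedures expects many older participants to have difficulty with the technology. Instrumented activity tracking requires the sensor to be removed and charged every day, and plans for periods without upload. If loss of the final week is related to how mobility developed after discharge, a complete-case change score can distort the association that the study is meant to estimate.

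**Working it through.** **1. Rows per patient.** The response is D = (mean daily distance, final week) − (mean daily distance, days 8–14). Each patient has one D. A patient-level random effect cannot be separated from residual error when each patient has one row. If either week is missing, D does not exist and the patient contributes nothing. The regression on D is then a complete-case analysis. A random centre effect could still be fitted, but it would not bring back patients without D.

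**2. The plan's own sample size.** Inputs from Sample size: slope 7.05 m per percentage point, predictor SD 35.36 points, outcome SD 1900 m, two-sided 5%, power 80%, dropout 10%, N = 500.

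- Slope × predictor SD = 7.05 × 35.36 = 249.3 m.
- Residual SD = √(1900² − 249.3²) = 1883.6 m.
- Noncentrality = 249.3 × √n / 1883.6, with n − 2 degrees of freedom.
- Evaluable patients = 500 × 0.9 = 450. Noncentrality = 2.808, power = 80.0%.
- Smallest n for 80% power = 451, and 451 / 0.9 = 501.1, rounded up to 502.

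Reading 1900 m as the residual SD gives 458, inflated to 509, and power 79.3% at 450. N = 500 therefore reproduces from one row per patient and takes no credit from a mixed model.

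**3. Power at fewer complete cases (illustration only).** The same formula at assumed numbers of patients with both weeks:

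| Complete cases (assumed) | Share of 500 lacking D | Power |
|---|---|---|
| 450 | 10% | 80.0% |
| 400 | 20% | 75.2% |
| 350 | 30% | 69.5% |
| 300 | 40% | 62.7% |

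This is ordinary loss of power with n. The documents give no figure for missing weeks, and the table leaves out any gain from covariates.

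**4. What the outcome rows are worth (illustrative simulation).** Assumed inputs: 500 patients; three time points; between-patient SD 1500 m and residual SD 1166 m, so total SD = √(1500² + 1166²) = 1900 m and intraclass correlation = 1500² / 1900² ≈ 0.62; true slope at the final time 7.05 and half of that at midterm; 34% of final values missing, depending on the observed change to midterm; 100 runs.

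| Analysis | Mean slope | Monte Carlo SE |
|---|---|---|
| Complete-case regression on D | 6.45 | 0.25 |
| Mixed model, three outcome rows | 7.12 | 0.26 |

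The change score falls short by (7.05 − 6.45) / 7.05 ≈ 9%, about 2.4 Monte Carlo standard errors. The three-row model is within simulation error of the truth. The protection comes from the intermediate row, which the stated response omits.

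**The case against.** The strongest reply is that the plan does foresee more than one outcome measure. Sample size speaks of adding further positively correlated outcome measures, the sensor records every day, and a change to month 8 can be estimated as a contrast in a mixed model of distances. This stands to the extent that a reader who inferred that a repeated-measures model is impossible here would go too far. The model is inconsistent with the stated response and not fully specified, but it can be built. The reply does not remove the contradiction. The further measures are unnamed, Statistical procedures fixes the response as the change for these very regressions, and listing baseline distance as a covariate fits a change-score regression rather than a model with baseline as an outcome row.

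A second reply is that the analysis plan can settle this. It can settle what is left open, but here the article fixes both the model and the response, and they disagree. Any analysis plan has to depart from one of them.

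A third reply is that harm is not shown. This stands in part. Participants are phoned every 2 weeks, and investigators follow up absent or strongly deviating data. Each window is a weekly average with no stated need for seven complete days. A complete-case regression is not biased under every mechanism, and the 9% above belongs to one assumed mechanism. A two-window endpoint is also a legitimate choice, for which the article gives reasons. The fault is the property claimed for it.

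**Conclusion.** The point holds as an internal contradiction in Statistical procedures. Under the stated response there is no within-patient repetition, patients lacking either week are dropped, and the cited robustness and the power gain expected from the mixed model are not available. The contradiction follows from the text alone. Its size cannot be read from the documents: the power table rests on assumed complete-case numbers, and the 9% attenuation on assumed variances and an assumed dropout mechanism.

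Three stronger conclusions that a reader might draw are not supported:

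- **That N = 500 is wrong.** It was derived from a one-row regression and reproduces on that basis.
- **That the plan wrongly claims cover for a missing degree of participation.** That predictor does rest on therapist forms, and a mixed model does not by itself handle a missing covariate. But the article limits its statement to repeated measurements, and the handling of unanswered forms or of patients without sessions may be left to the analysis plan.
- **That the 10% dropout allowance excludes patients with missing weeks.** The article does not define dropout.

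**What to change.** Choose one of two routes and state it before analysis.

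**Route A, keep the repeated-measures model (preferred).**
- Enter distances as outcome rows, for example mean daily distance in the day 8–14 week, a midterm week and the final week, or 4-weekly means.
- Fit patient as a random effect, with time, degree of participation, and participation by time.
- Name the association of participation with change from baseline to month 8, per percentage point, as the primary contrast.
- Do not also enter baseline distance as a covariate when it is an outcome row.
- Keep the two-window change score as a sensitivity analysis.

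**Route B, keep the change score.** Call the analysis a regression on one change per patient, and withdraw the repeated-measures wording and the missing-data claim for it. Remove the expectation of extra power from the mixed model.

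**Cost.** Route A needs no new data, because distance is recorded daily. It needs revised wording and some programming, and the time points and form of the time trend must be chosen. One limit has to be written down: participation is accumulated over all 8 months, so at earlier times the model would relate distance to therapy not yet given. Only the month-8 contrast should be interpreted. Route B costs only wording but leaves the complete-case loss in place.

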**Methods:**

The NeuroMoves study is intended as a national multicenter observational cohort study with 9 clinical sites in Germany. A total of 500 patients with mobility-restricting paralysis syndromes (i.e. stroke or SCI) are to be recruited during acute inpatient rehabilitation prior to discharge to the ambulatory setting. Patients will have 8 months of follow-up in the ambulatory setting. Three study visits at the clinical sites (baseline, midterm, and final) are planned at 4-months intervals. The baseline visit is scheduled at the end of the acute inpatient rehabilitation. During the visits, demographical data, neurological, functional, quality of life, and implementation measures will be assessed.

At baseline, each study participant receives an activity tracker (sensor for recording ambulatory mobility) along with a tablet computer for home use over the 8 months study duration. While mounted, the activity tracker records mobility data from which the daily distance covered by walking or wheelchair use can be calculated. Customized applications on the tablet computer remind the study participants to answer structured questionnaires about their health condition and treatment goals for physical therapy. Using the study participants’ tablet, therapists will be asked to answer structured questionnaires concerning treatment goals and therapeutic measures they have applied. The primary analysis concerns the association between mobility (daily distance covered) and the degree of participation-oriented rehab interventions. Further exploratory analyses are planned.

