#### Measures

After a potential candidate agrees to participate in the study, appropriate assessments (Table 1: NeuroMoves visit schedule; Fig. 2: study flowchart) are collected at three time points (baseline, midterm, final visit) within the 8-months observation period. The baseline visit takes place in the clinic at the end of inpatient care or within the first 6 weeks thereafter. For the midterm and final visits (and where required the baseline visit), study participants are asked to attend outpatient appointments at the respective study center.

**Table 1 Tab1:** NeuroMoves visit schedule: within the 8-months observation period, the following assessments are collected at 3 visits: International Standards for Neurological Classification of Spinal Cord Injury (ISNCSCI), Spinal Cord Independence Measure (SCIM) III, National Institutes of Health Stroke Scale (NIHSS), modified Rankin Scale (mRS), Barthel Index (BI), functional independence measure (FIM), modified Rivermead Mobility Index (mRMI), 10-m walking test (10mWT), Timed up and go Test (TUG), Wheelchair Skills Test Questionnaire (WST-Q), Wheelchair Questionnaire, Depressions Anxiety and Stress Scale (DASS), World Health Organization Quality of Life Brief Version and disabilities module (WHOQOL-BREF-DIS), Questionnaire of individual care networks

Assessment	Baseline	Midterm 4 months ±2 weeks	Final 8 months ±2 weeks
**Demographics**	**X**	**X**	**X**

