To minimize measurement inaccuracies for the sensor-based algorithms for movement or step detection, the sensor of the activity tracker is attached as follows: For wheelchair users, a clip device is attached to the wheel of the wheelchair allowing for easy fixation and removal of the sensor. For pedestrians, the sensor is attached to the shoelaces or shoe strips on the less affected leg via a clip device. In the case of borderline walkers, two clip devices are used: One is attached to the shoe of the less affected leg and the other to the wheel of the wheelchair. Since only one sensor is available per study participant, the study participants are requested to put the sensor into the clip of the device in use (either shoe or wheelchair). Based on the motion profiles recorded by the sensor, the activity tracker automatically recognizes the type of mobility (pedestrian or wheelchair).

At the end of each day, study participants must recharge the sensor by removing it from the clip and placing it on a wireless charger. If the sensor and the tablet computer are within Bluetooth transmission range during the charging process, the sensor data is automatically uploaded to the tablet. A wireless internet connection is required to upload the activity data from the tablet to the server of the study management system. Usually, this upload is scheduled once a day, but can also be delayed up to a week. The study participants are instructed accordingly at the baseline visit. Every 2 weeks, study participants are contacted by phone to clarify technical questions and problems.

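### The final week of primary outcome (1) is anchored to the 8-month clinic visit, so a participant who misses that visit but still transmits tracker data has no defined 8-month value

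*Protocol article*

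**What the plan says.** All references are to the protocol article.

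- **Outcome (Statistical procedures).** "the primary outcome (1) is defined as the change in the daily distance covered between baseline and final visit after 8 months".
- **Baseline window (same section).** "the daily distance averaged over the second week after start of mobility recording, i.e. day 8–14 after baseline". This is fixed by recording days.
- **Final window (same section).** "For the final mobility measurement, we will use the daily distance averaged over the final week prior to the last study visit". This is fixed by a visit.
- **The visit (Measures, Table 1).** The column heading is "Final 8 months ±2 weeks". For the midterm and final visits, "study participants are asked to attend outpatient appointments at the respective study center".
- **The measurement (Abstract, Methods).** Each participant has the tracker and a "tablet computer for home use over the 8 months study duration".
- **The upload (Instrumented activity tracking).** "Usually, this upload is scheduled once a day, but can also be delayed up to a week". It runs from sensor to tablet to server, and no clinic attendance is involved.
- **Missing data (Statistical procedures).** Linear mixed models are described as robust "with respect to missing data of repeated measurements (under the assumption of missing at random").

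**The concern.** The outcome is mobility at home, measured remotely. Its start is set by the recording calendar, but its end is set by whether and when the participant comes to the study centre. Someone who does not come in at month 8 has no qualifying week under the stated rule, even if the server holds a full set of days around that date.

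This matters because the reason for not coming may be the outcome itself. The study asks who loses mobility after discharge. The Background section says that mobility declines after stroke rehabilitation and that fractures from falls and pressure injuries are common in the chronic course. Such events are credible reasons for missing an outpatient appointment. If they are the reason, the missing final values sit disproportionately among decliners. A complete-case comparison would then understate deterioration and pull the slope on degree of participation towards zero. Missing at random becomes a stronger assumption than it needs to be, since some of the missing values may have been recorded.

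There is a smaller wording problem. The final-window sentence refers to the last study visit and not to the 8-month visit, which leaves it unclear what applies to a participant whose last visit was the midterm.

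**Working it through.** **1. The two windows side by side**

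| | Baseline week | Final week |
|---|---|---|
| Anchor | Start of recording, days 8–14 | Last study visit |
| Needs a further clinic visit? | No | Yes |
| Value defined if that visit is missed? | Not applicable | No |

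Nothing in the measurement process requires the right-hand column to differ from the left.

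**2. The plan's own sample size**

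Inputs from Sample size: slope β = 7.05 m per percentage point, predictor SD = 35.36, outcome SD = 1900 m, two-sided 5%, power 80%, dropout 10%, N = 500.

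- β × SD of X = 7.05 × 35.36 = 249.29 m, and its square is 62,144.5.
- With 1900 m as total SD, the residual variance is 1900² − 62,144.5 = 3,547,855.
- n = (1.960 + 0.842)² × 3,547,855 / 62,144.5 = 7.849 × 57.09 = 448.1. Dividing by 0.90 gives 498.
- With 1900 m as residual SD, n = 7.849 × 3,610,000 / 62,144.5 = 455.9. Dividing by 0.90 gives 507.

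The stated 500 is reproduced, with about 450 evaluable (500 × 0.90).

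**3. Power if lost final values are recovered** (noncentral t, 1900 m as total SD)

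| Evaluable | 400 | 425 | 450 | 475 | 500 |
|---|---|---|---|---|---|
| Power | 75.2% | 77.7% | 80.0% | 82.1% | 84.0% |

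The step from 450 to 500 is an upper limit. It assumes that every one of the 10% lost missed the visit with the tracker still sending. If half did, the figure is 475 and 82.1%.

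**4. Illustrative bias from outcome-dependent loss**

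Simulation, with X = 100 × Beta(0.5, 0.5) and Y = 7.05 X + normal error with the SD above. A stated share of patients is deleted and a simple regression is fitted to the rest. The documents give no selection strength, so each pattern is an assumption.

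| Loss pattern | Total loss | Slope (true 7.05) | Upward shift in mean change |
|---|---|---|---|
| 70% of the loss in the worst 30% | 5% | about 6.9 | about 70 m |
| 70% of the loss in the worst 30% | 10% | about 6.8 | about 140 m |
| Loss risk 30% in the worst fifth, 5% elsewhere (0.2 × 30% + 0.8 × 5% = 10%) | 10% | about 6.6 | about 150 m |
| Exactly the worst decliners | 5% | about 5.8 | about 210 m |
| Exactly the worst decliners | 10% | about 5.1 | about 370 m |

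**5. Scale**

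The planned standard error of the slope is about 1900 / (35.36 × √450) = 2.53. Moderate selection at 10% moves the slope by 0.3 to 0.5, or about 0.1 to 0.2 standard errors. The extreme case moves it by about 2.0, or about 0.8 standard errors.

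**The case against.** **The plan does not take a month-4 value.** A reader might infer that the window follows the last visit attended, so that a participant last seen at midterm has the month-4 week analysed as the 8-month outcome. The documents do not support this. The same paragraph defines the outcome up to the final visit after 8 months, Sample size repeats baseline to 8 months, and Table 1 lists three visits with the last at 8 months. The natural reading is the scheduled final visit. What remains is an ambiguity that a few words would remove.

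**Missed-visit rules belong in the full protocol or SAP.** That is fair for a rule that is merely absent, and the article condenses a fuller document. Here, however, the article states the anchor, and the anchor is what is questioned.

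**The mixed model deals with missing data.** It may help. Sample size foresees further correlated outcome measurements, and the figures above ignore that by using complete cases. They are therefore bounds and do not describe the planned analysis. The model still relies on missing at random, and observing the value is better than assuming it.

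**The affected group may be small.** This stands. The 10% dropout is not broken down by cause and may include withdrawal, death and stopping use of the device. A bed-bound or readmitted patient may not be clipping in, charging and uploading the sensor. Fortnightly calls, and contact when data deviate or stop, may also limit loss. A reader might conclude that the rule removes the patients with the greatest decline, but no document shows that decliners attend less often.

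**The ±2-week tolerance** is ordinary and is not a problem in itself.

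**Conclusion.** The point holds as a weakness in how the primary endpoint is anchored. A remotely measured outcome has a final window that depends on a clinic visit, so a participant who is still transmitting and misses that visit has no defined 8-month value.

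Whether this biases the result depends on two things the documents do not give: how many participants miss the visit while still transmitting, and how strongly non-attendance tracks decline. If the whole 10% dropout arose this way and were analysed as complete cases, the slope would be about 6.6–6.8 under moderate selection and about 5.1 in the limiting case, against 7.05. Full recovery would be worth at most about 4 points of power (80.0% to 84.0%). The moderate shifts are small against the standard error, and the shifts in mean change bear on descriptions of deterioration more than on the primary association. The case for changing the rule rests on its low cost and on needing less from missing at random, and not on a demonstrated large bias.

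**What to change.** Define the final mobility week by study day, for example the 7 days ending at 8 months after baseline, for every participant still transmitting, whether or not the final visit takes place. Add that a week before the midterm or an early-termination visit never serves as the 8-month value. Sites should ask participants who cannot attend to keep recording through that week and return the equipment afterwards, and should note the reason for non-attendance during the existing fortnightly calls.

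The cost is a short addition to the outcome definition and a site instruction, because the equipment and upload route are already in the home. There are two small downsides: the window may lie up to about 2 weeks from the clinic assessments, and some devices come back later. The planned sample size does not change.

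### The protocol article contradicts itself on which goals are rated at the end of a prescription cycle; if only highly ranked goals are requeried, its raw sum score for goal attainment mixes attainment with the number of goals

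*Protocol article*

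**What the plan says.** Goal attainment in patients and in health care providers is the fourth of the four primary outcomes.

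- **Start of a cycle** (Patient-reported treatment goal attainment): "an 11-item (5-point ordinal scale for each item) questionnaire will pop up to select between 11 prespecified treatment goals".
- **End of a cycle, same section:** "If it will be the last session of a prescription cycle, the participant will be asked to evaluate the same 11 items". A separate global item follows: "Moreover, the participant will be asked to rate the overall satisfaction of goal attainment on a 5-point ordinal scale".
- **End of a cycle, Statistical procedures:** "Subjectively highly ranked treatment goals are subject to requery at the end of each prescription cycle".
- **Scoring, Statistical procedures:** "Sum scores of items (item on 5-point ordinal scale) indicate the degree of goal attainment". The text gives no cut-off for a high rank, no fixed number of goals and no division by the number of items.
- **Whose score:** "Primary outcome (4) represents goal attainment analysis related to either patients or therapists, respectively". Therapists complete the same 11-item list at the start of a cycle. For the end of the cycle the therapist section reads "Additionally, at the last treatment session, the therapist will be asked about the treatment setting" and goes on to measures and intensity; it does not spell out a second rating of the goals.
- **Use:** "Results serve for further exploratory analyses, e.g. as explanatory variable for functional outcomes, quality of life measures, etc".

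**The concern.** Either all 11 items are rated at the end of a cycle, or only those that the rater had ranked highly. The two rules imply different query logic in the tablet app and different data sets. A rating that was never requested cannot be recovered at analysis.

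The scoring sentence then meets a different problem under each rule. If only highly ranked goals are requeried, the natural reading is that the sum runs over those goals. Their number, k, can vary between patients, between cycles of one patient, and between patient and therapist. A total over a varying number of items is not a measure of the degree of attainment alone. If all 11 items are rated, the number of items is fixed, but the total includes items that were not goals for that person.

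The score stands for a named primary outcome and bears on the stated objective about whether providers' treatment goals can be achieved. It is also meant to be reused as an explanatory variable, so any distortion carries into those analyses.

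**Working it through.** The article states no figure for primary outcome (4), so there is none to reproduce.

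**1. The two end-of-cycle rules**

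| | Patient-reported section | Statistical procedures |
|---|---|---|
| Items rated at end of cycle | all 11 | highly ranked goals only |
| Number of items | 11 for everyone | k, not fixed |
| Score | not stated there | sum of 5-point items |

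**2. Range of the sum over k goals.** The article gives five ordinal levels but no numerical codes, so both common codings are shown.

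- Coded 1 to 5: the sum runs from k to 5k. For k = 1 it is 1 to 5, for k = 3 it is 3 to 15, for k = 5 it is 5 to 25, for k = 11 it is 11 to 55.
- Coded 0 to 4: the sum runs from 0 to 4k.

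**3. Can the ranking reverse?** Take the top code as fully attained.

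- Coded 1 to 5: two goals fully attained give 2 × 5 = 10; eleven goals at the lowest rating give 11 × 1 = 11.
- Coded 0 to 4: two goals fully attained give 2 × 4 = 8; eleven goals at the second-lowest level give 11 × 1 = 11. Eleven goals at the lowest level now give 0, and three goals fully attained (3 × 4 = 12) exceed 11. Reversals are fewer but do not disappear.

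**4. Same attainment, different k.** At the middle level on every item, k = 2 and k = 11 score 2 × 3 = 6 and 11 × 3 = 33 (1 to 5), or 2 × 2 = 4 and 11 × 2 = 22 (0 to 4).

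**5. How much of the score is k?** The article gives no distribution of k, so this simulation is illustrative. All inputs are assumed: 200,000 patients; k uniform over the stated range and independent of attainment; true attainment normal with mean 3 and SD 0.5 or 1.0; item noise SD 0.8; items rounded and clipped to 1 to 5. Each cell gives R² at SD 0.5, then at SD 1.0.

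| Spread of k | Sum with k | Sum with attainment | Per-goal mean with attainment |
|---|---|---|---|
| 1 to 11 | 0.86, 0.69 | 0.08, 0.22 | 0.55, 0.82 |
| 2 to 6 | 0.72, 0.51 | 0.15, 0.37 | 0.54, 0.81 |
| 3 to 5 | 0.47, 0.28 | 0.30, 0.58 | 0.57, 0.82 |
| fixed at 11 | 0, 0 | 0.79, 0.93 | 0.79, 0.93 |

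R² between the per-goal mean and k is about 0 throughout. The last row treats all 11 items as relevant to everyone.

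**6. If all 11 items are summed.** Every person's range is 11 to 55 (or 0 to 44), and k plays no part. Each item carries 4 of the 44 points of range, or 1/11, about 9%, whether or not it was a goal. The list contains both walking and wheelchair mobility. The section Instrumented activity tracking expects pedestrians who rarely or never use a wheelchair, and wheelchair users who cannot walk or walk only in therapy. For such people at least one item may be irrelevant and still enters the total.

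**7. Check of the repair.** The examples in step 3 become, as percent of maximum, 10/10 = 100% against 11/55 = 20% (1 to 5), and 8/8 = 100% against 11/44 = 25% (0 to 4). The order is then correct under either coding.

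**The case against.** The best defence has four parts.

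- **The article does not say in so many words that the sum covers only requeried goals.** The instrument description is explicit about 11 items, and on that reading the dependence on k vanishes. This stands as a limit: the goal-count defect is conditional. It does not remove the contradiction. One could also suppose that all 11 items are asked and only the highly ranked ones scored, but then the sum again depends on k.
- **The item coding is assumed.** This stands. The 0 to 4 coding removes the starkest reversal, but not all of them.
- **Scoring detail is often left to a full protocol, an analysis plan or the questionnaire supplement, none of which is shown.** Anchors, a not-applicable option, the cut-off and any scaling may be set there, and their absence here is not the finding. Two statements in the article that disagree on what is asked, and a stated sum rule, are not omissions.
- **The consequences are limited.** The abstract names the primary analysis as mobility against participation-oriented intervention, and the sample size rests on outcomes (1) and (2). The overall satisfaction item does not depend on k, although the article does not make it the attainment score.

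A reader might infer that the score simply measures how many goals were chosen. The documents do not support that: the sum mixes number and attainment, and number dominates only if k varies widely. A reader might also infer that severely impaired patients would look more successful. Nothing in the article links severity to the number of goals.

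**Conclusion.** The contradiction over which items are rated at the end of a cycle is firm and needs no assumption.

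The scoring problem is conditional. If only highly ranked goals are requeried and the sum is left unscaled as stated, the score for primary outcome (4) depends on k as well as on attainment, for patients and therapists alike. Under the assumed inputs, k accounts for 28 to 47% of the variance of the sum when it varies over 3 to 5, and 69 to 86% when it varies over 1 to 11; the true spread is unknown. If all 11 items are rated and summed, this problem is absent, and the remaining weakness is that items which were not goals count in full.

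Severity is moderate. Goal attainment is a named primary outcome and is to be reused as an explanatory variable, but its use is exploratory and it does not drive the sample size.

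**What to change.** 1. Reconcile Statistical procedures with the questionnaire description, and check that the app's query logic matches. Confirm in the same check what the therapist rates at the last session.
2. Requery all 11 items at the end of each cycle. This keeps every scoring option open.
3. Replace the raw sum by the mean rating, or percent of maximum, over the goals that the same rater ranked highly at the start of that cycle. State the cut-off for a high rank on the 5-point scale and the item coding.
4. Report k for each rater and cycle.

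A sum over all 11 items would also remove the dependence on k, but would keep the weight on items that were not goals. The cost is a sentence or two of scoring text and a software check. The statistical price is slight: a per-goal mean is less precise when few goals are ranked highly, which reporting k makes visible.
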